### Study participants

The study population includes a subset of patients with CKD stages G4-G5 and patients on KRT in the Netherlands. The inclusion and exclusion criteria are mentioned in Table 1. Of note, patients will be eligible whether they have a history of COVID-19 or not.

**Table 1 Tab1:** Inclusion and exclusion criteria

*Inclusion criteria*	
1. Age of 18-80 years 2. Capable of understanding the purpose and risks of the study, to be fully informed and to give informed consent 3. Either - eGFR < 30 ml/min/1.73m^2^ but not on dialysis or with a kidney transplant - Haemodialysis or peritoneal dialysis - Kidney transplant recipient at least 6 weeks after transplantation	
*Exclusion criteria (≥ 1)*	
•Patients who opted out for the national dialysis (RENINE) and kidney transplantation (NOTR) registries.	

*eGFR* Estimated glomerular filtration rate

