### Outcome definitions

For an overview of the clinical endpoints in this study we refer to Table 3.

**Table 3 Tab3:** Clinical endpoints LESS-CoV-2 study

*Primary endpoint*	
Incidence (per person-year) of COVID-19 in a two-years period after SARS-CoV-2 vaccination in patients with CKD stage G4-G5 or on KRT.	
*Secondary endpoints*	
Efficacy	
• The antibody based immune response to SARS-CoV-2 vaccination at 28 days after SARS-CoV-2 vaccination.	
• The durability of the antibody response at 6 months after SARS-CoV-2 vaccination	
Safety	
• Incidence of mortality	
• Incidence of AEs of specific interest as defined by (inter) national authorities	
• Incidence of a combined endpoint of acute rejection or graft failure in kidney transplant recipients	
• Incidence of HLA antibodies defined as cPRA > 5% in dialysis patients on the waiting list for their first kidney transplantation	
*Exploratory endpoints*	
Vaccination coverage rates	
Disease severity in patients who develop COVID-19, assessed as	
• Hospitalization	
• ICU admission	
• Mechanical ventilation	
PROMs in patients on dialysis	
SARS-CoV2 genotype in patients with COVID-19 (in case available)	

*COVID-19* Coronavirus Disease 2019, *SARS-CoV-2* Severe Acute Respiratory Syndrome Coronavirus-2, *CKD* Chronic Kidney Disease, *KRT* Kidney Replacement Therapy, *AEs* Adverse Events, *HLA* Human Leukocyte Antigen, *cPRA* Calculated Panel Reactive Antibody, *ICU* Intensive Care Unit, *PROMs* Patient Reported Outcome Measures

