### Antibody measurement

We will analyse the presence of antibodies against the RBD of the SARS-CoV-2 S-protein (IgG anti-RBD antibody) using the Sanquin anti-SARS-CoV-2 RBD IgG ELISA assay [15]. This is an indirect ELISA using microtiter plates coated with RBD and detection by monoclonal mouse anti-human IgG. The antibodies against the RBD are the primary constituent of the humoral immune response after SARS-CoV-2 vaccination. We combine this test with a Sanquin anti-SARS-CoV-2 nucleocapsid protein (NP) bridging ELISA. This test is an indirect ELISA using microtiter plates coated with NP and detection by biotin-labelled NP. Both antibodies against RBD and NP arise after a natural COVID-19 infection. In contrast, vaccination only induces antibodies to RBD, since NP is not part of any of the currently used vaccines. Combining these two tests enables us to differentiate between antibodies after vaccination or after previous COVID-19 infection.

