#### Analysis of secondary endpoints

##### Efficacy - Antibody response

Participants will be classified as responders or non-responders [17]. Number and proportion of responders and non-responders at day 28 will be reported for each patient population. Pearson chi-2 test will be performed to assess whether antibody response differ between patient groups. In subsequent sensitivity analyses we will perform multiple regression analyses correcting for possible differences in age and sex between the patient groups. Additionally, in kidney transplant recipients we will investigate whether time after transplantation, and the different immunosuppressive regimens are associated with response rate.

To assess durability of response within each patient group, we will report and compare response at day 28 with response at month 6 after vaccination. Comparison will be made using McNemar test.

The association between antibody response after SARS-CoV-2 vaccination and protection against COVID-19 will be examined for each patient group separately. For this, we will compare the antibody response at 28 days after vaccination in patients who develop COVID-19 with the antibody response in patients who did not develop COVID-19. Similar comparison will be made at 6 months after vaccination. We will examine this by use of the t-test or if more appropriate a non-parametric test. Subsequently, in a logistic regression model using Youden’s index, a cut-off in the antibody response at 28 days will be defined to serve as a correlate of protection against COVID-19.

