## Discussion

In the LESS-CoV-2 study we will assess the efficacy and safety of the mRNA-1273, BNT162b2, ChAdOx1 nCoV-19 and Ad26.COV2.S SARS-CoV-2 vaccines in Dutch patients with CKD stages G4-G5, on dialysis or after kidney transplantation.

We expect to determine an antibody response cut-off value which allows to predict protection against COVID-19 breakthrough infection after completion of SARS-CoV-2 vaccination. This contributes to the establishment of surrogate endpoints which will facilitate the development and approval of new vaccines [18]. In this study, we will identify non-responders by means of an insufficient antibody response after SARS-CoV-2 vaccination. This population can be offered a booster vaccine or an alternative vaccine to assess whether or not a sufficient antibody response can still be achieved.

Furthermore, we will address the safety of SARS-CoV-2-vaccination in patients with severe kidney insufficiency and in those that are treated with immunosuppressive drugs. Since these patients were not sufficiently represented in the large registration studies of the various vaccines, specific AEs associated with kidney failure and its treatment may not have been recognized so far. In addition, rare but possibly harmful AEs must be searched for in pharmacovigilance studies after widespread distribution of the vaccines. Recent reporting of vaccine-induced immune thrombotic thrombocytopenia caused by the ChAdOx1 nCoV-19 and Ad26.COV2.S SARS-CoV-2 vaccines is a possible example of such a rare complication [19]. It is essential to collaborate with large registry studies to be able to detect rare SAEs in patients with kidney disease. Different SARS-CoV-2 vaccines are administered to our subjects, and for that reason we will monitor the development of immunisation against HLA-antigens, allograft rejection and/or kidney transplant failure following SARS-CoV-2 vaccination.

Considering that items such as mental QoL, anxiety and depression may be positively influenced by vaccination, it is highly relevant to monitor the effect of SARS-CoV-2 vaccination on patient reported outcome measurements (PROMs). In our cohort of dialysis patients PROMs have been monitored since 2019. During the study we will further monitor the course of mental health of vaccinated and non-vaccinated dialysis patients and compare this to pre-COVID-19 pandemic era and the COVID-19 pandemic era without vaccines.

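### The day-28 antibody response mixes vaccine response with earlier infection, and the McNemar comparison at month 6 can hide loss among responders

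*Protocol article*

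**What the plan says.** Table 3 (Outcome definitions) names two antibody endpoints: "The antibody based immune response to SARS-CoV-2 vaccination at 28 days after SARS-CoV-2 vaccination" and "The durability of the antibody response at 6 months after SARS-CoV-2 vaccination".

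The section Efficacy - Antibody response fixes their analysis. "Participants will be classified as responders or non-responders", the groups are compared by Pearson chi-square, and sensitivity analyses are "multiple regression analyses correcting for possible differences in age and sex between the patient groups". For durability, "we will report and compare response at day 28 with response at month 6 after vaccination", using McNemar's test within each group.

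Elsewhere in the article:
- Study participants: "patients will be eligible whether they have a history of COVID-19 or not".
- Antibody measurement: natural infection produces both anti-RBD and anti-nucleocapsid (NP) antibody, vaccination only anti-RBD. "Combining these two tests enables us to differentiate between antibodies after vaccination or after previous COVID-19 infection".
- Study design: both antigens are measured, with samples at 28 days and 6 months. Table 2 records COVID-19 before vaccination.
- Analysis of primary endpoint: the incidence analyses are repeated with and without evidence of prior infection. This sentence refers back to the primary-endpoint analyses and comes before the antibody section.
- Discussion, on non-responders: "This population can be offered a booster vaccine or an alternative vaccine". No timing is given.

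**The concern.** The endpoints are the response to vaccination and its persistence. The measured marker, anti-RBD, also rises after infection, so a patient infected earlier can be classed as a responder whatever the vaccine did. If infection history differs between the CKD G4-G5, dialysis and transplant groups, the chi-square test can show a group difference that comes from exposure rather than vaccine response. Adjusting for age and sex does not remove it.

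For durability, McNemar's test sets losses (responder to non-responder) against gains (non-responder to responder). Gains without a new stimulus should be few. Infection or an extra dose between the two samples creates them, and they offset real losses. The question behind the endpoint is what share of responders keep their response, and the net comparison does not answer it directly.

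At stake are two secondary endpoints, and the ranking of patient groups drawn from them.

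**Working it through.** The article gives no expected response rate, power or alpha for the antibody endpoints, so there is no figure of its own to reproduce beyond 3 × 4,000 = 12,000, which adds up. All rates below are assumptions. Only n = 4,000 per group comes from the article (Study enrolment).

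**Day 28.** Let r be the response in uninfected patients, f the share previously infected and q the response among them. The observed share is (1 − f)r + fq, and the inflation is f(q − r).

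| r | q | f | Observed | Inflation (points) |
|---|---|---|---|---|
| 50% | 95% | 5% | 52.25% | 2.25 |
| 50% | 95% | 20% | 59.0% | 9.0 |
| 60% | 95% | 5% | 61.75% | 1.75 |
| 60% | 95% | 20% | 67.0% | 7.0 |
| 95% | 99% | 5% | 95.2% | 0.2 |
| 95% | 99% | 20% | 95.8% | 0.8 |

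**Group comparison.** Take two groups with the same r = 60% and q = 95%, but 5% and 15% previously infected.
- Observed: 0.95 × 0.60 + 0.05 × 0.95 = 61.75%, and 0.85 × 0.60 + 0.15 × 0.95 = 65.25%.
- Standard error of the difference at 4,000 per group: √[(0.6175 × 0.3825 + 0.6525 × 0.3475)/4,000] = 0.01076.
- 0.035/0.01076 − 1.96 = 1.29, so a two-sided 5% test declares a difference about 90% of the time, although vaccine response is identical.

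**Durability.** Assume 4,000 patients, 60% responders at day 28 (2,400) and 10% true loss (240). With no new stimulus, month 6 is 2,160/4,000 = 54.0%. Assume infection makes 80% of would-be non-responders positive and an extra dose converts 50% of the day-28 non-responders who receive it. McNemar's chi-square is (losses − gains)²/(losses + gains).

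| Interim infection | Non-responders given an extra dose | Losses | Gains | Observed month 6 | Chi-square |
|---|---|---|---|---|---|
| 0% | 0% | 240 | 0 | 54.0% | 240.0 |
| 5% | 0% | 240 × 0.96 = 230 | 1,600 × 0.04 = 64 | 55.8% | 94.1 |
| 10% | 0% | 240 × 0.92 = 221 | 1,600 × 0.08 = 128 | 57.7% | 24.7 |
| 5% | 20% | 230 | 1,600 × (1 − 0.96 × 0.90) = 218 | 59.7% | 0.4 |
| 5% | 50% | 230 | 1,600 × (1 − 0.96 × 0.75) = 448 | 65.4% | 69.8 (a gain) |

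Infection alone shifts the month-6 figure by 1.8 to 3.7 points here, and the decline remains clear. A smaller true loss is easier to hide: at 5% loss (month 6 = 57.0%) and 10% interim infection there are 110 losses and 128 gains, 60.4% observed and chi-square 1.3. With 90% responders and 10% loss, month 6 is 81.0% and the observed figure runs from 81.8% (5% infection, no extra doses) to 84.2% (5% infection, 50% given an extra dose).

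Retention among responders barely moves. At 5% interim infection it is 1 − 230.4/2,400 = 90.4% against a true 90.0%, whatever share of non-responders receive extra doses.

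**The case against.** The strongest reply is that this is an article, and rules on analysis sets, interim infection and extra doses may stand in a full protocol or analysis plan that is not shown. The endpoint is worded as response to vaccination, and the paired assays were chosen to separate the two sources, so the intention is evident. All vaccinated patients are also a legitimate real-life population. McNemar's test is valid for paired binary data, and its table contains the losses among responders.

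Much of this stands:
- A reader might infer that the plan states that interim-infected and boosted patients are counted. It does not; their inclusion follows only from the absence of a rule.
- A reader might infer that boosters will turn waning into an apparent rise. The Discussion mentions an extra dose only as a possibility, without timing relative to month 6, and the large shifts rest on that assumption.
- A reader might infer that the figures do not measure vaccine response at all. They measure it mixed with infection, and the mixture matters little near the ceiling.
- Restricting durability to patients still NP-negative at month 6 selects on a post-vaccination event. If waning predicts infection, dropping breakthrough cases removes those who waned and overstates durability.

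What does not stand is that nothing is fixed. The test, the adjustment covariates and the population wording are all stated, and the prior-infection split is written for the primary endpoint but not here. An unseen rule would have to change the analysis as published.

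**Conclusion.** The point holds in limited form. Followed as written, the day-28 response and its comparison between groups confound vaccine response with infection history. The inflation is about 2 to 9 points for an uninfected response of 50-60% with 5-20% previously infected, and under 1 point for a response near 95%. It therefore matters most in whichever group responds poorly. The Background expects a lesser response in transplant recipients, but the documents give no infection rates by group, so the direction and size of any spurious group difference are not established.

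For durability, the net comparison can mask loss among responders. The effect of interim infection alone is modest in points, though enough to hide a small decline. A large effect requires extra doses in non-responders before month 6, which the article neither schedules nor rules out. The calculations show what the stated analysis permits; they do not predict what will be observed.

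**What to change.** 1. **Day 28.** Make the main response analysis and the group comparison in participants without evidence of prior infection (no recorded COVID-19 and NP-negative at day 28). Show previously infected participants separately, matching the split already written for the primary endpoint.
2. **Durability.** Report the proportion of day-28 responders who retain response at month 6, with a confidence interval. Censor, or classify separately, those with NP seroconversion, reported COVID-19 or an extra dose before the month-6 sample.
3. **Keep the all-participant McNemar result alongside**, and say why: excluding breakthrough infections can itself overstate durability, so the two results should be read together.

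The cost is a change of wording, a somewhat smaller sample for the main analyses and one extra sensitivity analysis. NP results at both samples, COVID-19 history, COVID-19 during follow-up and vaccination status are already to be collected.

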## Methods and analysis

### Study design

This is a prospective national observational cohort study which includes all kidney patients who were vaccinated against SARS-CoV-2 in the Dutch vaccination programme. Currently available vaccines in the Netherlands are the mRNA-1273 (Moderna), BNT162b2-mRNA (Pfizer), ChAdOx1 nCoV-19 (AstraZeneca) and Ad26.COV2.S (Janssen) vaccines [5–8]. Patients with CKD stages G4-G5 or on KRT received prioritization as medical high-risk group and predominantly received the mRNA-1273 vaccine in the Dutch vaccination programme. To assess the antibody dependent immune response after vaccination, blood samples will be collected at 28 days and at 6 months after the second vaccination with a home-based finger prick test. Antibody measurement will include both the receptor binding domain (RBD) of the spike (S) antigen and the nucleocapsid (N) antigen [15]. Combining these antibody measurements allows to distinguish a natural infection from an antibody response after S1-based vaccination.

Questionnaires will be obtained during a two-year follow-up period to assess the incidence of COVID-19 or (serious) adverse events ((S)AEs) after vaccination. The study events are demonstrated in Fig. 1. The questionnaires are shown in the supplemental materials.

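### The correlate-of-protection cut-off rests on the day-28 antibody level alone, in a model without time, although COVID-19 is followed for two years and a month-6 level is collected

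*Protocol article*

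**What the plan says.** All places are in the protocol article.

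- **Sampling** (Study design): "blood samples will be collected at 28 days and at 6 months after the second vaccination". No later sample is planned.
- **Outcome follow-up** (Study design): "Questionnaires will be obtained during a two-year follow-up period to assess the incidence of COVID-19". The primary endpoint in Table 3 (Outcome definitions) is "Incidence (per person-year) of COVID-19 in a two-years period after SARS-CoV-2 vaccination".
- **Correlate analysis** (Efficacy - Antibody response): within each patient group, "we will compare the antibody response at 28 days after vaccination in patients who develop COVID-19 with the antibody response in patients who did not", by t-test or a non-parametric test. Then: "Similar comparison will be made at 6 months after vaccination". Neither comparison has an outcome window.
- **Cut-off** (same section): by logistic regression with Youden's index, the plan is that "a cut-off in the antibody response at 28 days will be defined to serve as a correlate of protection against COVID-19". The month-6 level plays no part in it.
- **Durability** (Table 3): "The durability of the antibody response at 6 months after SARS-CoV-2 vaccination" is a secondary endpoint, tested with McNemar's test on responder status.
- **Intended use** (Discussion): the cut-off is to predict protection against breakthrough infection and to help establish surrogate endpoints. The same section says that non-responders can be offered a booster or another vaccine.
- **Assay** (Antibody measurement): natural infection induces antibody to RBD as well as to the nucleocapsid protein.

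**The concern.** The cut-off analysis joins a level measured once, about a month after vaccination, to an outcome that may occur up to two years later, and the model has no time axis. Three things follow from the wording.

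1. Early and late infections carry equal weight, whatever has happened to the antibody level in between. Patients who die or leave uninfected are grouped with the protected. The primary analysis of the same outcome uses Cox regression with cause-specific hazards, so the study already has the tool that this step drops.
2. The study measures whether the level lasts and foresees re-vaccination of low responders, but the cut-off takes neither into account.
3. The month-6 comparison is not limited to infections after the month-6 sample. A patient infected in month 3 may have a high RBD level at month 6 because of that infection, which would make high antibody look unprotective.

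A cut-off without a horizon, partly shaped by decline and re-vaccination, is a weak basis for the surrogate-endpoint use that the Discussion describes.

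**Working it through.** The article gives no event count, power figure or effect size for this analysis, so there is nothing of its own to reproduce. The check is whether, and when, the day-28 level loses information over two years. **Every parameter below is an assumption.**

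**Algebra.** Let L(t) be the log10 level t months after the day-28 sample, L(t) = L28 - d·t, with monthly hazard h(t) = 0.0015·exp(-(L(t) - 2)). If d is the same in everyone, the hazard ratio between patients A and B is exp(-(L28,A - L28,B)) at every t. The day-28 level then keeps its full value, and waning alone causes no dilution. With a floor, L(t) = max(0, L28 - d·t), two patients at the floor have hazard ratio 1 whatever their day-28 levels. From a mean of 2.5, the floor is reached at 2.5/0.15 = 16.7 months when d = 0.15, and at 2.5/0.10 = 25 months when d = 0.10.

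**Simulation 1: floor and spread of decline.** L28 has mean 2.5 and SD 0.7, and no one is re-vaccinated. The true hazard ratio per 10-fold level is exp(-1) = 0.37. For infections before month 6, the day-28 odds ratio was 0.36-0.38 and the AUC 0.69. For all two-year infections:

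| Monthly decline, mean (SD) | Floor | Odds ratio | AUC |
|---|---|---|---|
| 0.10 (0.03) | no | 0.35 | 0.694 |
| 0.15 (0.03) | no | 0.32 | 0.70 |
| 0.15 (0.03) | yes | 0.60 | 0.60 |
| 0.10 (0) | yes | 0.44 | not reported |
| 0.15 (0) | yes | 0.61 | not reported |
| 0.10-0.15 (0.08) | no | not reported | 0.66-0.67 |

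The floor does most of the work: at decline 0.15 (SD 0.03), 83% of patients are at it by month 23. A modest spread of decline without a floor does no harm. A wide spread costs a little.

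**Simulation 2: re-vaccination regardless of level.** L28 has SD 0.8, mean decline is 0.12 per month, the hazard ratio is 0.5 per log10 of current level, and there is no floor. The six-month AUC is 0.66 throughout. The 24-month AUC without re-vaccination is 0.71, 0.70 and 0.66 for decline SD 0, 0.05 and 0.1, so it is never lower than at six months. With 80% re-vaccinated in months 5-9 it is 0.62-0.63. Cumulative infection in these runs is very high (46% to 61% at 24 months), so AUC is the fairer comparison than the odds ratio.

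**Simulation 3: re-vaccination of low responders.** L28 has mean 2.5 and SD 0.8, decline is 0.12 per month (SD 0-0.1), with a floor at 0 and a hazard ratio of 0.5 per log10.

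- No boosters: AUC 0.65 (to month 5) against 0.61-0.64 (two years); odds ratio about 0.50 against 0.54-0.61.
- Boosters to 80% of the lowest fifth: AUC 0.65 against 0.58-0.60; odds ratio 0.65-0.71 at two years. The Youden cut-off rises by about 0.25-0.3 log10, that is 10^0.25 = 1.8-fold to 10^0.3 = 2.0-fold.

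The cut-off shift is the least certain figure. In simulation 2 the six-month cut-off alone ranged from -0.12 to -0.26 across runs.

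**Does the month-6 level help?** In further runs with assumed inputs it predicted later infections as well as or better than the day-28 level. With boosters to low responders, the late AUC was 0.60-0.82 against 0.53-0.60.

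**Events.** In simulation 1 about 1% of patients are infected before month 6. With the intended 4,000 per group (Study enrolment), that is 4,000 × 0.01 = 40 events per group.

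**The case against.** - **Waning is not predicted.** A reader might infer that the study itself expects antibody to wane by month 6. No section says so; durability is an endpoint to be measured. This objection stands.
- **Two years is inferred.** It is the follow-up and primary-endpoint window, and the antibody section states no window of its own. An article may leave that to a fuller plan, so the missing window alone would be a weak point. What remains is printed: day 28 only, logistic model, Youden's index.
- **The later sample is used.** A month-6 comparison is planned, and this partly answers the concern. But it does not feed the cut-off and, as worded, does not exclude earlier infections. The nucleocapsid assay could identify such patients, but the comparison does not say that it will be used for this.
- **A day-28 cut-off is legitimate.** An early post-vaccination level can be a useful predictor of later risk, and the Discussion wants to identify non-responders. That is true if the cut-off is labelled as a day-28 value for a stated horizon, and none is stated.
- **Dilution is not certain.** This stands too. With uniform decline and no floor the simulations show none, and the larger effects depend on an assumed floor or on boosters.
- **Narrow windows cost events, and updating has limits.** Restricting the day-28 analysis to the first six months could leave some 40 events per group. The month-6 level is in turn carried forward to the end of follow-up. Both limits stand and belong in the report.

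**Conclusion.** The concern holds in a limited form. As written, the cut-off ignores when infection occurs, when follow-up ends, the month-6 level and re-vaccination, and the month-6 comparison allows infection to raise the level that is supposed to predict it. These faults follow from the text.

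Whether they distort the result materially depends on facts that the document does not give. Under assumed inputs, the two-year AUC of the day-28 level ranges from no loss (uniform decline, no floor) to a fall from about 0.65 to 0.58-0.60 (boosters to low responders, with a floor). In that last case the cut-off moves by up to about two-fold, with considerable noise. A reader might conclude that the correlate is diluted and the cut-off stale; the documents support only that this can happen under the conditions named.

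The change is worth making because it uses samples already planned and the regression method already chosen for the primary endpoint.

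**What to change.** In Efficacy - Antibody response, replace the two-group tests and the logistic model with a Cox model of time to COVID-19, per patient group, that:

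1. starts at the day-28 sample;
2. uses the antibody level as a time-updated covariate, replaced by the month-6 value when that sample is taken;
3. counts only infections after the sample in use, so that no level is related to an infection that preceded it;
4. censors at death and at re-vaccination. Because a low level may prompt re-vaccination, the level must be in the model for this censoring to be defensible.

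Derive the cut-off from this model and report it with the sample it belongs to and a stated horizon, for example day 28 to month 6, and a fixed period after month 6.

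**Cost:** analysis wording only, with no new samples or visits. Infections after re-vaccination no longer contribute, few events will support the early-window cut-off, and the month-6 level is still carried forward because no later sample exists. The report should give the event count behind each cut-off.

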#### Analysis of primary endpoint

Incidence rates of COVID-19 within 2 years after vaccination will be reported for each study population separately and incidence rates will be compared. Primary comparisons are comparisons of COVID-19 incidence rates in vaccinated patients versus non-vaccinated patients and versus the vaccinated general population. These comparisons will be made separately for patients with CKD stages G4-G5 or on KRT. For comparison of incidence rates, we will calculate crude hazard ratios. Vaccine efficacy will be reported as 100 × (1- hazard ratio). We will calculate model adjusted hazard ratios using multivariable Cox-regression, in case of imbalance in study populations regarding relevant characteristics, such as age, sex, comorbidity, kidney replacement modality and use of immunosuppressive agents. Cause specific hazard ratios will be estimated to account for competing risk of mortality. Starting date of follow-up will be the date of second vaccination in vaccinated patients. Starting date of follow-up in non-vaccinated patients will be the same date (or +/− 7 days from date of vaccination) as date of vaccination in the matched vaccinated patients to account for changes in incidence of COVID-19 over time. Non-vaccinated patients will be censored at the day of vaccination in case they are vaccinated before the end of follow-up. The aforementioned analyses will be repeated in patients with and patients without evidence of prior infection. Among vaccinated patients, incidence rates will also be compared across the various vaccines that will be used. For this purpose, vaccinated patients with CKD stages G4-G5 or on KRT and general population again will be analysed separately.

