##### Safety

Incidence rates of (S)AEs, mortality, acute rejection, graft failure or HLA antibodies will be calculated and compared across patient groups in analyses similar to analysis of the primary outcome.

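### The antibody-protection analysis treats COVID-19 as a yes/no outcome over two years and ignores time at risk and death, although the primary analysis handles death as a competing risk for the same event

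*Protocol article*

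**What the plan says.** The relevant text is in the protocol article.

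- **Efficacy - Antibody response.** For each patient group separately, day-28 antibody response in those who develop COVID-19 is compared with "the antibody response in patients who did not develop COVID-19", and the same is done at month 6. On the test: "We will examine this by use of the t-test or if more appropriate a non-parametric test". A logistic regression with Youden's index follows, in which "a cut-off in the antibody response at 28 days will be defined to serve as a correlate of protection against COVID-19".
- **Analysis of primary endpoint.** For the same event: "Cause specific hazard ratios will be estimated to account for competing risk of mortality".
- **Safety.** Safety outcomes are "compared across patient groups in analyses similar to analysis of the primary outcome". No such sentence covers the antibody-protection analysis.
- **Table 3 (Outcome definitions).** The primary endpoint is a rate over two years: "Incidence (per person-year) of COVID-19 in a two-years period after SARS-CoV-2 vaccination in patients with CKD stage G4-G5 or on KRT".
- **Discussion.** "We expect to determine an antibody response cut-off value which allows to predict protection against COVID-19 breakthrough infection". The cut-off is also meant to help establish surrogate endpoints for new vaccines.

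**The concern.** A t-test, a rank test, a logistic model and Youden's index all need each patient to be a case or a non-case. None of them knows how long a patient was observed. On the plain wording, someone who dies without COVID-19 is a patient who did not develop it and joins the comparison group. Death ends the chance of infection; it is not evidence that the antibody level was protective. Short follow-up raises the same problem.

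The protocol recognises this for its primary endpoint but names a method that ignores it for the antibody analysis. What is at stake is the proposed correlate of protection. If patients with low antibody levels also die more often, uninfected deaths collect at the low end of the comparison group, and low antibody looks less harmful than it is. Because the analysis is run per patient group, the amount of distortion can also depend on each group's mortality.

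**Working it through.** The article gives no event rate, mortality rate or power figure for this analysis, so there is no stated number to reproduce. The only inputs taken from it are two years of follow-up and 4000 patients per group (Study enrolment). **All rates below are assumptions.**

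**Check 1: low versus high responders**

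Assume 20% low responders (800 against 3200) and COVID-19 hazards c of 0.10 (low) and 0.05 (high) per year, a true hazard ratio of 2.0. With death hazard d, the two-year proportion with COVID-19 is c/(c+d) × (1 − exp(−2(c+d))). The proportion dying uninfected is d/(c+d) × (1 − exp(−2(c+d))).

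Without deaths: low 1 − exp(−0.20) = 0.1813; high 1 − exp(−0.10) = 0.0952. Odds ratio = (0.1813/0.8187)/(0.0952/0.9048) = 2.11.

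With deaths kept as non-cases:

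| Death hazard, low / high | COVID-19, low / high | Died uninfected, low / high | Odds ratio | Shift in SE of log OR |
|---|---|---|---|---|
| 0.25 / 0.12 | 0.1438 / 0.0848 | 36% / 20% | 1.81 | 1.25 |
| 0.15 / 0.08 | 0.1574 / 0.0881 | 24% / 14% | 1.93 | 0.73 |
| 0.05 / 0.03 | 0.1728 / 0.0924 | 9% / 6% | 2.05 | 0.23 |

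First row, low responders: 0.10/0.35 × (1 − exp(−0.70)) = 0.1438. The standard error is the usual square root of summed reciprocal cell counts; there it is 0.119, and ln(2.105/1.814)/0.119 = 1.25.

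If antibody had no effect on COVID-19 (equal c in both groups), the odds ratio would be about 0.87 to 0.88, 0.93 and 0.98 in the three rows.

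**Check 2: the cut-off itself**

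Assume log antibody is standard normal within a group. COVID-19 hazard is 0.03 or 0.10 per year at mean antibody, rising 1.5- or 2-fold per SD lower antibody. Mean death hazard is 0.02 to 0.20 per year, rising 1.0- to 2.0-fold per SD lower antibody. Numerical integration over two years gives, for COVID-19 at 0.03 per year and 1.5-fold per SD:

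| Deaths per year, gradient per SD | Cut-off, no deaths (SD) | Cut-off as planned (SD) | OR per SD, no deaths | OR per SD as planned |
|---|---|---|---|---|
| 0.10, none | −0.19 | −0.19 | 0.656 | 0.658 |
| 0.10, 1.6-fold | −0.19 | −0.14 | 0.656 | 0.696 |
| 0.10, 2-fold | −0.19 | −0.09 | 0.656 | 0.716 |
| 0.20, 2-fold | −0.19 | 0.00 | 0.656 | 0.766 |

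Across the grid, the cut-off moves by at most about 0.01 SD when death is unrelated to antibody level. When low responders die more often it moves upward, by about 0.01 to 0.2 SD. Patients who died first make up about 4% of the comparison group at 0.02 deaths per year and 31% to 36% at 0.20.

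**Check 3: would dropping the dead repair it?**

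No. With 0.10 deaths per year and a 2-fold gradient, excluding them gives an odds ratio of 0.602 per SD against 0.656 without deaths, so the association is overstated.

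**The case against.** **The bias depends on a premise that is not in the article.** A reader might infer that the cut-off is biased because low responders are more likely to die. The article does not say so. Its Background links weaker vaccine response to uraemia and immunosuppression, not to death. If death is unrelated to antibody level, the cut-off hardly moves. This stands, so the distortion can only be stated conditionally.

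**The article does not say that uninfected deaths are kept or called protected.** That is correct. It follows from the wording and from methods that need a yes/no outcome, but no explicit rule is given.

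**The shift in the cut-off is smaller than its own sampling error.** In simulations with 4000 patients under the same kind of assumptions, the shift was 0.05 SD against a sampling SD of about 0.3. With more frequent COVID-19 and a steeper gradient it was 0.03 against about 0.15. In the extreme case it was 0.18 against 0.28 to 0.37. This stands as a statement of size. It also rules out claiming that patient groups would get visibly different cut-offs through mortality alone. It does not excuse the method, because systematic error does not shrink with sample size and the odds ratio is affected too.

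**Low antibody could be made to look protective.** A reader might infer this as a general result. It occurs only if antibody has no true effect, and at low mortality the odds ratio is then about 0.98. With a true hazard ratio of 2.0, none of the three scenarios falls below 1.81.

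**Details belong in the analysis plan.** A rule for deaths commonly would. Here, however, the article names the groups, tests, model and cut-off criterion, and an analysis plan that follows them inherits the problem.

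**Conclusion.** The point holds as an inconsistency with a conditional consequence. The article fixes a time-free yes/no analysis over two years for an event whose competing risk of death it handles properly in the primary analysis.

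If lower antibody level goes with higher mortality, the association is diluted and the cut-off rises. Under the assumed rates the effect ranges from negligible (0.23 SE; 0.01 SD) to material for the association (1.25 SE) and modest for the cut-off (about 0.2 SD), the upper end needing high mortality strongly related to antibody level. The article gives no rates with which to place these patient groups in that range. A cause-specific model does not require knowing which case applies.

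This concerns a secondary, predictive analysis and leaves the primary vaccine-efficacy comparison untouched. It should be corrected because the cut-off is put forward as a correlate of protection and the correction is cheap.

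**What to change.** In Efficacy - Antibody response, replace the ever/never comparison and the logistic model as follows.

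1. Model time from the day-28 sample to COVID-19 with a cause-specific Cox model, with log antibody level as covariate and censoring at death and at loss to follow-up, in line with the primary analysis. For the month-6 comparison, start time at the month-6 sample.
2. Derive any cut-off from the cause-specific hazard by antibody level, or from a time-dependent ROC/Youden analysis that censors deaths, using inverse-probability weights that may depend on antibody level and age.
3. Do not take the cut-off from the ever/never classification, from a data set with the dead removed, or from cumulative incidence that keeps deaths in the denominator. The last brings the dilution back: in the first scenario of Check 1 it gives 14.4% against 8.5%, and so the same odds ratio of 1.81.

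The cost is a change of analysis wording, slightly more analysis work and a less simple cut-off derivation. Dates of COVID-19 and death are already needed for the primary analysis.
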